## Discussion

Post-stroke cognitive impairment is highly prevalent all over the world [16]. It significantly impairs patients’ participation in rehabilitation, engagement in daily activities, and their quality of life [55]. Meanwhile, the high economic burden that stroke rehabilitation imposes on family and society is growing [56]. Moreover current therapies, mainly CT and pharmacological treatment, lack sufficient evidence to support their effectiveness due to the complexity of cognitive impairment management [6]. The recent use of combined therapy has increasingly attracted attention, offering a new prospect in PSCI treatment [17].

Acupuncture is considered to be effective in improving cognition and has the advantages of being simple, convenient, efficient, and inexpensive, without severe adverse effects [20, 57]. A systematic review [58] has proposed that acupuncture improves cognitive function impairment in patients with PSCI, but the lack of high quality research has prevented the development of evidence-based recommendations for clinical practice. This review also recommends that future clinical trials should focus on the effect of acupuncture treatments combined with a second treatment, aiming to find the most cost-effective therapy combination that promotes the greatest improvement in stroke rehabilitation.

Previous studies have been limited by random methodology and small sample sizes [26, 27]. Thus, a prospective, multicenter, large sample, single-blinded, randomized controlled trial designed under strict systematic operational and high quality practices is needed to evaluate whether a therapeutic regimen of TCM rehabilitation leads to a more effective improvement in PSCI.

A notable difference between our study and former studies is that this trial will investigate, some domain-specific cognitive functions as well as general cognitive state. According to one article, patients with PSCI will mainly exhibit dysfunctions in attention, memory, and executive function [6]. To evaluate domain-specific cognitive function various measures were selected: the TAP to assess attention, the WMS-RC to evaluate memory, and the TMT and Stroop test to measure executive function. In this study, detailed information on performance in multifarious tasks designed for CT will be recorded, allowing an insightful outcome analysis by taking into account the severity of and inter-relationships among the cognitive deficits in various domains. Besides, fMRI and ERPs will be included in this trial as objective indicators of cognitive function [59–61]. Since many stroke patients who suffer from PSCI and movement disorders cannot understand and/or perform tasks adequately, resting-state fMRI was chosen over tasking-state fMRI for this study [62]. Meanwhile, ERP P300 and resting-state fMRI make it possible to provide a potential mechanism for the therapeutic effects of this trial’s approach, and to further explore the relationship between cognitive functional networks and brain structure, thus allowing the researchers to investigate the relationship between subjective scales and objective indicators.

Adhere to the SPIRIT guidelines, a prospective, multicenter, large sample, randomized controlled trial with blinded assessments has been designed [63]. This protocol design has several strengths: (1) it is a multicenter trial that will be carried out in seven inpatient and outpatient stroke rehabilitation units, which enhances the study’s external validity and sample representativeness; (2) to guarantee quality, all staff in the study are required to complete training on standard operating procedures of the study protocol before recruiting; (3) this study is centrally randomized to guarantee adequate allocation concealment and blinded assessment of results [64]; (4) a 12-week intervention and 24-week follow-up assessment can provide reliable long-term effect evidence for a therapeutic regimen of TCM rehabilitation treatment and its health economics in PSCI clinical practice.

However, this protocol design also has potential limitations: for example, it is not a double-blinded, placebo-controlled trial. From the perspective of evidence-based medicine, randomized, double-blind, placebo-controlled trials are the best the trials that render the highest evidence quality, but their feasibility is a major difficulty in non-pharmacological research areas [65]. Considering the ethics and participants’ adherence, blinding seems difficult for acupuncture in a clinical study, thus randomized, double-blinded, placebo-controlled trials may be impossible. Considering these facts, this trial attempts to reduce possible bias through blinding both outcome assessors and data analyst. Further, potential spontaneous recovery at the early stage of stroke may have the confounding effects on the trial.

To conclude, this trial aims to evaluate, under strictly systemized operational and high quality practices, whether a therapeutic regimen of TCM rehabilitation can effectively improve cognitive functions recovery after stroke under strict standard operational practices. If this trial is successfully carried out and renders high quality evidence to support a therapeutic regimen of TCM rehabilitation for PSCI management, this low cost and feasible therapy could be implemented on a larger scale in clinical and community settings.

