### Inclusion criteria

This trial’s participants should meet all the following criteria: (1) Signed informed consent by the patient or their guardian to participate in this trial; (2) Present stroke diagnosis according to the fourth national academic conference on cerebrovascular disease’s Diagnostic Criteria for All Kinds of Cerebrovascular Disease [28], and confirmed by computed tomography or magnetic resonance imaging; (3) Mini-Mental Status Examination (MMSE) score ≤24; (4) First ever stroke and within one year post-stroke; (5) Aged between 45 to 75 years; and (6) Patient should be conscious, with stable vital signs.

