### Randomization and allocation concealment

Stratified-block randomization would be applied into the study, which will take each center as a stratification factor. Each eligible participant will be randomly assigned to either the intervention group or control group according to 1:1 equal proportion rule. The sequence of random allocation will be generated using the PLAN sentences of the statistical software SAS 9.3 (SAS institute Inc., Cary, NC, USA), by an independent statistician who will not be involved in this trial from the Center of Evidence Based Medicine, FJTCM. Also, the sequence of random allocation will be concealed to outcome assessors and the statistical analyst. Then, the eligible participants will be informed of their allocation result by the project manager via telephone after their baseline information has been assessed, and the therapists (including acupuncturist and cognitive therapists) will be notified of the allocation and arrange the allocated treatment directly for the patient.

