### Baseline tests

Descriptive data will be collected before randomization. The descriptive data includes gender, age, height, weight, nationality, education level, employment status, clinical syndrome (left or right hemiplegia), and the type, frequency, and location of the stroke at diagnosis. The National Institute of Health Stroke Scale, an 11-item evaluation tool to assess stroke severity, will be applied at baseline to determine whether the two groups are consistent before the intervention [30]. All subjects will be assessed with the following measures: the severity of cognitive impairment will be assessed using the Mini-Mental Status Examination (MMSE), as well as the Montreal Cognitive Assessment (MoCA); attention function will be measured with the Test of Attentional Performance (TAP); memory function will be tested with the Wechsler Memory Scale-Revised in Chinese (WMS-RC); executive function will be evaluated with the Stroop test, as well as the Trail Making Test; motor function will be measured with the Fugl-Meyer Motor Assessment Scores; activities of daily living (ADL) will be assessed with the Modified Barthel Index (MBI); and quality of life will be evaluated with the 36-Item Short Form Health Survey (SF-36). Moreover, the functional condition of the brain is examined by using a resting-state functional magnetic resonance imaging (fMRI) and event-related potentials (ERP).

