### Statistical methods

All data will be analyzed using SAS version 8.2 (SAS institute Inc., Cary, NC, USA) by an independent blinded statistician. A statistical significance level of 0.05 will be used. For statistical description, continuous variables will be presented for each group using the mean ± standard deviation for normal distribution, and median and interquartile range for non-normal distribution. Categorical variables will be presented by using proportions with their standard error. In order to compare the primary and secondary outcomes between groups, measured at baseline, post-intervention and post-follow-up, the t-test or Mann–Whitney U test will be used for continuous variables and the Pearson chi-squared or Fisher’s exact test will be used for categorical variables. Non-parametric tests, Pearson chi-squared test, or Fisher’s exact test will be used for expressing changes in effect sizes of primary and secondary outcomes between groups before and after treatment, and during the follow-up period (at 12 weeks and 24 weeks).

To adjust the confounding influence if necessary, a general linear model or linear regression will be applied for dependent continuous variables, and a logistic regression model for dependent categorical variables. The analysis of the primary outcome will be expressed by using full analysis set with the principle of intention-to treat and the per-protocol set. The analysis of the secondary outcomes will be performed using the per-protocol set. The analysis of AE will be undertaken by using a chi-square test or Fisher’s exact test. Lastly, the economic evaluation will be assessed using cost-effectiveness analysis. Missing data will be imputed by the last observation carried forward rules.

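### Time since stroke is not among the listed baseline items and has no fixed place in the MMSE comparison, although the protocol names early spontaneous recovery as a threat; the cost is modest lost precision and an open choice to adjust, not bias

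*Protocol article*

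**What the plan says.** All places are in the protocol article.

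- **Inclusion criteria.** The time window is "First ever stroke and within one year post-stroke". No minimum interval is given. The only criterion touching the earliest phase is "Patient should be conscious, with stable vital signs", which is a clinical state and not a time limit. Recruitment covers both inpatient and outpatient rehabilitation units.
- **Discussion, limitations.** The authors state that "potential spontaneous recovery at the early stage of stroke may have the confounding effects on the trial". For the limitation on blinding they describe a countermeasure (blinded assessors and analyst). For spontaneous recovery they give none.
- **Randomization and allocation concealment.** Stratified blocks are used, "which will take each center as a stratification factor". No other factor is named.
- **Baseline tests.** "The descriptive data includes gender, age, height, weight, nationality, education level, employment status", followed by "clinical syndrome (left or right hemiplegia), and the type, frequency, and location of the stroke at diagnosis". The NIH Stroke Scale is added to check that the arms are comparable. Time since stroke does not appear.
- **Statistical methods.** For comparing outcomes between groups, "the t-test or Mann–Whitney U test will be used for continuous variables". A general linear model or linear regression may be applied if adjustment for confounding is judged necessary. What would make it necessary, and for which covariates, is not said.

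**The concern.** The entry window mixes patients who may still be recovering spontaneously with patients close to a year out. On the protocol's own premise, natural recovery is an early phenomenon, so time since stroke should predict MMSE change in both arms. It is the one prognostic factor the document singles out as a threat, yet what the document fixes does not use it.

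Three things are at stake:

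1. **Precision.** Variation in natural recovery stays in the residual of an unadjusted test.
2. **Chance imbalance.** If one arm happens to enrol earlier after stroke, an unadjusted comparison cannot correct for it. Unless the variable is tabulated, a reader cannot see it either.
3. **An open analytic choice.** A rule that adjusts only when it seems necessary lets the decision, and the covariates, depend on the data.

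Interpretation is also affected. Week 36 is about 8.3 months after the start of treatment (36/52 × 12), so for entry between 0 and 12 months after stroke the long-term visit falls anywhere from about 8 to 20 months post-stroke. Without the variable, a reader cannot tell which phase the result describes.

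**Working it through.** **1. Reproduce the planned size, to have a scale.** Inputs from Sample size: SD 1.5, alpha 0.05 (taken as two-sided), power 90%, and n = 2(u_α + u_β)²σ²/δ².

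- With δ = 3.52 as worded, n = 4 per group.
- With δ = 3.52 − 3 = 0.52: 2 × (1.960 + 1.282)² × 2.25 / 0.2704 ≈ 175, close to the stated 173.

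So 0.52 points is the difference the stated size implies, and it serves as the yardstick here. (The wording of the effect size is a separate matter.) At 173 per arm:

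- SE = 1.5 × √(2/173) = 0.161
- power = Φ(0.52/0.161 − 1.96) = 89.7%

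**2. Chance imbalance.** In SD units of time since stroke, the difference in arm means has standard error √(2/173) = 0.108, so 95% of imbalances lie within ±1.96 × 0.108 = ±0.21 SD. This assumes simple randomisation.

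**3. Translate to MMSE.** Let r be the correlation between time since stroke and MMSE change. The document does not give it, so a range is shown.

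- Shift at the 95% limit = r × 1.5 × 0.21
- Residual SD after adjustment = 1.5 × √(1 − r²)

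| Assumed r | Shift at 95% limit (points) | Share of 0.52 | n per arm after adjustment | Power at 173 per arm |
|---|---|---|---|---|
| 0 | 0 | 0% | 175 | 89.7% |
| 0.1 | 0.03 | 6% | 174 | 90.0% |
| 0.2 | 0.06 | 12% | 168 | 90.8% |
| 0.3 | 0.09 | 18% | 160 | 92.2% |
| 0.5 | 0.16 | 30% | 132 | 96.1% |

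**4. Is the shift bias?** No. Its variance under randomisation is (r × 1.5)² × 2/173, and the squared standard error of the unadjusted difference is 1.5² × 2/173. The ratio is r². At r = 0.3, 9% of the sampling variance comes from imbalance in this factor, and that 9% is already counted in the standard error. The shift column and the power column therefore describe the same quantity in two ways and must not be added together.

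**The case against.** The strongest reply is that the trial already has the main safeguard. A concurrent 1:1 randomised control receives the same conventional treatment and cognitive training, so natural recovery occurs in both arms and cancels in expectation. If the SD of 1.5 describes the enrolled population, the unadjusted test keeps its type I error. This stands. A reader might take the Discussion's word confounding at face value and infer a biased treatment effect; the design does not support that.

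Other points, and what remains of each:

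- **Adjustment is not absent.** Statistical methods allows a linear model, and covariate lists are often left to an analysis plan, which is not shown here. It would be wrong to say that the protocol ignores adjustment, or that it has singled out time since stroke for omission, since no covariate is named. What remains is what the document does fix: an unadjusted comparison, with adjustment conditional on an undefined judgement. The analyst's blinding to arm labels reduces the risk of a selective choice but does not remove it, because coded results can still be compared with and without adjustment.
- **The baseline list may not be exhaustive.** It is introduced as what the data include, and onset timing has to be known to apply the one-year criterion. A reader might infer that the date is not collected. The document shows only that it is not listed.
- **Very early entry may be rare.** A reader might infer that patients enter in the acute phase. The article does not say so. The absence of a lower limit permits early entry, but recruitment through rehabilitation units, the stability criterion and a baseline assessment one to two weeks before treatment make it less likely.
- **Stratification by centre alone is a legitimate choice**, and nothing here requires changing it.

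**Conclusion.** The point holds in a limited form. The protocol names a prognostic threat, admits patients across the window in which it operates, does not list the variable that measures it, and fixes an unadjusted comparison with an open-ended option to adjust. The consequences are lost precision, possible chance imbalance and a data-dependent choice, not systematic bias.

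The size is modest. For r of 0.2 to 0.3, power at 173 per arm rises by about 1 to 2.5 percentage points, and a chance imbalance at its 95% limit moves the estimate by 0.06 to 0.09 points, which is 12% to 18% of the implied 0.52-point effect. Much larger gains can be produced. For example, if half the patients were early entrants gaining 2 points more than the rest, the factor would explain (2²/4)/2.25 = 44% of the variance. But neither that split nor that gap comes from the document, so the figure should not be relied on.

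The results rest on SD 1.5, δ = 0.52, a two-sided 5% test and the assumed r. Any further gain from adjusting for baseline MMSE and centre is not counted. The change is worth making because it is nearly free, not because the trial is otherwise unsound.

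**What to change.** 1. Add time from stroke onset to randomisation to the items under Baseline tests, using the date needed for the one-year inclusion criterion, and report it by arm.
2. In Statistical methods, make the primary MMSE comparison at weeks 12 and 36 a prespecified linear model with treatment, baseline MMSE, centre and time since stroke (for example as log days). This replaces both the unadjusted test and the conditional adjustment rule for that outcome.
3. Optionally, add one treatment-by-time-since-stroke interaction, labelled exploratory.

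Eligibility, recruitment and randomisation stay as they are. The cost is one derived field, obtainable for patients already enrolled because the date bears on eligibility, and a change of main method from a two-sample test to a regression model. That change is more than one added term, so it should be documented and fixed before unblinding, which the Blinding section places after all 36-week data are collected.

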## Trial status

Participant enrollment started in July 2014. The trial is expected to be completed by the end of December 2016.

## Abbreviations

ADL: Activities of daily living
AE: Adverse event
CT: Cognitive training
DSMB: Data and Safety Monitoring Board
ERP: Event-related potentials
FJTCM: Fujian University of Traditional Chinese Medicine
fMRI: Functional magnetic resonance imaging
MBI: Modified Barthel Index
MMSE: Mini-Mental State Examination
MoCA: Montreal Cognitive Assessment
PSCI: Post-stroke cognitive impairment
SF-36: 36-Item Short Form Health Survey
TAP: Test of attentional performance
TCM: Traditional Chinese Medicine
TMT: Trail Making Test A and B
WMS-RC: Wechsler memory scale-revised in Chinese
